## Abstract

**Background:**

In recent years, cognitive training has gained popularity as a cost-effective and accessible intervention aiming at compensating for or even counteracting age-related cognitive declines during adulthood. Whereas the evidence for the effectiveness of cognitive training in general is inconsistent, processing speed training has been a notable successful exception, showing promising generalized benefits in untrained tasks and everyday cognitive functioning. The goal of this study is to investigate why and when processing speed training can lead to transfer across the adult lifespan. Specifically, we will test (1) whether training-induced changes in the rate of evidence accumulation underpin transfer to cognitive performance in untrained contexts, and (2) whether these transfer effects increase with stronger attentional control demands of the training tasks.

**Methods:**

We will employ a multi-site, longitudinal, double-blinded and actively controlled study design with a target sample size of *N* = 400 adult participants between 18 and 85 years old. Participants will be randomly assigned to one of three processing speed training interventions with varying attentional control demands (choice reaction time, switching, or dual tasks) which will be compared to an active control group training simple reaction time tasks with minimal attentional control demands. All groups will complete 10 home-based training sessions comprising three tasks. Training gains, near transfer to the untrained tasks of the other groups, and far transfer to working memory, inhibitory control, reasoning, and everyday cognitive functioning will be assessed in the laboratory directly before, immediately after, and three months after training (i.e., pretest, posttest, and follow-up, respectively). We will estimate the rate of evidence accumulation (drift rate) with diffusion modeling and conduct latent-change score modeling for hypothesis testing.

**Discussion:**

This study will contribute to identifying the cognitive processes that change when training speeded tasks with varying attentional control demands across the adult lifespan. A better understanding of how processing speed training affects specific cognitive mechanisms will enable researchers to maximize the effectiveness of cognitive training in producing broad transfer to psychologically meaningful everyday life outcomes.

*Trial registration* Open Science Framework Registries, registration https://doi.org/10.17605/OSF.IO/J5G7E; date of registration: 9 May 2022.

## Background

Fluid cognitive abilities such as processing speed, attentional control, and reasoning decline with progressing age [1]. In later adulthood, these profound changes can affect everyday life functioning and life satisfaction [2]. Thus, it is critical to identify evidence-based and accessible interventions that can counteract these declines. In recent years, cognitive training interventions have gained popularity as a cost-effective and easy-to-administer option for maintaining cognitive health into later life. The rationale of cognitive training is straightforward: By targeting and improving specific core cognitive processes, improvements in these basic cognitive processes can generalize—or transfer—to untrained contexts also drawing on these processes. However, the empirical evidence for the effectiveness of cognitive training in eliciting such broad transfer effects is overall weak [3]: Although most training interventions induce large and robust performance gains in the trained tasks [4], these training effects often do not transfer to untrained tasks or everyday life functioning [5, 6]. A notable successful exception appears to be training interventions targeting processing speed and attentional control, which have been shown to transfer to older adults' everyday functioning and may even delay the onset of dementia [for a review, see 7]. These successful training interventions typically require participants to react as quickly and as accurately as possible to a stimulus, often in combination with attentional control demands such as the inclusion of a secondary task. However, the cognitive mechanisms underlying these training and transfer effects are yet unclear [3, 8]. The goal of this study is to identify the key mechanisms of when and why processing speed training can elicit transfer.

### Attention control demands in processing speed tasks

The speed with which people process information is a key cognitive ability that is strongly related to a wide range of cognitive domains [9], including working memory [10] and fluid intelligence [11]. Moreover, declines in processing speed have been proposed to account for much of the cognitive changes observed in aging [12]. Hence, interventions successful in increasing speed have great potential to yield broad cognitive benefits. Yet, tentative evidence suggests that targeting processing speed alone may not suffice for inducing transfer effects [13, 14]. Indeed, successful speed training interventions [7, 15] often additionally demand attentional control, which is the ability to maintain an operative goal, and goal-relevant information, in the face of distraction [16].

Existing processing speed training tasks vary in the extent to which they involve attentional control. For example, a typical processing speed task with minimal attentional control demands is the simple reaction time (RT) task, in which participants are asked to press a key as soon as a stimulus appears on screen. In contrast, in a choice RT task, participants are asked to decide between two alternatives, such as whether a simple geometric shape is blue or green, as quickly and as accurately as possible. Different to simple RT tasks, choice RT tasks require goal maintenance and distraction avoidance [17], although these attentional control demands are still relatively low as participants can focus their attention on a single task.

Attentional control demands are higher when multitasking [18], that is, when two (or more) tasks are processed sequentially (switching tasks) or simultaneously (dual tasks). In task switching, multiple choice RT tasks are performed sequentially, often in random order with a cue indicating the upcoming task (task-cueing paradigm). For example, participants may be asked to switch between categorizing simple geometric shapes by their color (e.g., deciding whether the object is blue or green) or by their shape (e.g., deciding whether the object is curvy or spiky). Switching between the two tasks requires focusing on the currently relevant task while inhibiting the other, currently no longer relevant task, a process which involves maintaining, updating, inhibiting, and activating a different task in working memory [19, 20] as well as using proactive control strategies [21]. In dual tasks, two tasks are presented and performed simultaneously; for example, participants are instructed to make both decisions related to color and shape on the same stimulus at the same time. Hence, in addition to the attentional demands of task switching, participants need to divide their attention between the two tasks, which requires task coordination and optimizing attentional resource allocation between two simultaneous and independent task processing streams and their concurrence for limited processing capacities [15, 22]. Yet, we do not know conclusively how the attentional control demands of a task affect the effectiveness of training in producing broad transfer gains. Therefore, in this study, we will systematically compare the effects of training with choice RT tasks, switching tasks, and dual tasks to an active control group practicing simple RT tasks. If attentional control demands are critical in inducing broad transfer, we would expect to find larger transfer gains the greater the training tasks’ attentional control demands.

### Estimating cognitive processes underpinning processing speed performance: the diffusion model

Processing speed performance is commonly measured with mean RTs and/or the proportion of correct responses (accuracy) in speeded tasks. However, relying only on mean RTs and accuracy when evaluating processing speed gains during training is problematic for at least three reasons. One concern is the psychometric validity of these measures. Specifically, RT distributions typically have a positively skewed, asymmetric shape. Therefore, the mean and other point estimates are a poor representation of that distribution. Accuracies are not a good alternative either, because adults tend to perform near ceiling in these tasks and, thus, usually only little variance in performance is observed. A second concern is that people may differ in their speed-accuracy trade-off, that is, the extent to which they emphasize giving speedy or accurate responses. Furthermore, these preferences may change across the lifespan and over time in a training context. This complex relation between the speed and accuracy distribution complicates their interpretation. Finally, mean RTs and accuracies do not directly assess the psychological processes assumed to underlie the decision-making process.

The diffusion model (Fig. 1) is a computational approach that addresses these three concerns and estimates parameters representing the psychologically meaningful processes involved in speeded cognitive tasks [23]. This model assumes that each decision involves continuously accumulating information—a mix of evidence and noise—that is indicative of two alternative options. Once the stimulus has been encoded, the decision-making process begins at a starting point *z*, with the drift rate *v* reflecting the rate of accumulating evidence until a threshold is reached. The decision-making process ends when this threshold is surpassed and, thus, a critical upper or lower boundary is reached, resulting in executing the response. The boundary separation *a* reflects response caution: People who tend to respond more conservatively (i.e., base their decision on more evidence) will have wider boundaries, whereas the boundary separation will be narrower in people who tend to respond more liberally. To map task performance onto these processes, computational routines are used to estimate the parameters by fitting the model to a data set. Critically, the diffusion model jointly considers RTs and accuracy, thereby accounting for individual differences and change in speed-accuracy trade-offs.

**Fig. 1 Fig1:**
[figure not shown]
Simplified Illustration of the Diffusion Model and Its Main Parameters. *Note*. After stimulus encoding, information accumulation begins at the starting point *z* and proceeds with a mean drift rate *v* until either response option A or B is reached, followed by response execution. The observed RT is the sum of the decision time and the time required for non-decision processes (*Ter*) such as stimulus encoding and response execution

Decomposing task performance into theoretically meaningful diffusion model parameter estimates can provide valuable insights into the mechanisms of transfer across the lifespan. First, the diffusion model parameters reflect trait-like properties of cognitive processes that are temporally stable and task-general [24], yet they are sensitive to age-related differences [25] and manipulations of attentional control demands [26]. These properties render the diffusion model parameters ideally suitable for investigating associations between intervention-specific effects and individual differences. Furthermore, previous research has shown that individual differences in drift rate are associated with mental abilities such as fluid intelligence [10, 27], making it a prime candidate mechanism potentially underlying the transfer effects observed in previous processing speed training studies. In the present study, we will be able to directly test this hypothesis by distinguishing training-induced changes in drift rate from such in response caution and non-decision components and evaluate how change in these cognitive processes contribute to transfer effects.

This preregistered study will follow methodological best practices [28–30] by including an active control group to account for test–retest and placebo effects, using multiple tasks to assess abilities on the latent level, and testing a sample large enough to provide adequate statistical power. Furthermore, our conclusions will be based on Bayesian inference, allowing for gauging the strength of evidence for the presence as well as the absence of any hypothesized effects and relationships.

### Objectives

The overarching goal of this study is to identify the cognitive processes improved by training speed tasks and how they are affected by varying attentional control demands across the adult lifespan. This study goes beyond previous cognitive training studies by using diffusion modeling to estimate theoretically and psychologically meaningful components of information processing and relating them to gains in untrained contexts. For this purpose, we pursue the following objectives:Examine how extensive speed training affects the cognitive processes involved as reflected by changes in diffusion model parameters, and whether these changes in cognitive processes vary across the lifespan.Investigate how changes observed in these cognitive processes are related to transfer effects in working memory, inhibitory control, reasoning, and everyday cognitive functioning, and whether these changes are maintained after the end of the training intervention.Determine how attentional control demands of training interventions modulate these effects.

### Hypotheses

#### Hypothesis 1

(training gains): On average, participants in the three experimental conditions will show larger pre-post improvements in their respective training tasks than participants in the active control condition.

#### Hypothesis 2

(near transfer gains): On average, participants in the three experimental training conditions will show larger pre-post improvements in the untrained processing speed training tasks of the other experimental conditions than participants in the active control condition.

#### Hypothesis 3

(far transfer gains): On average, participants in the three experimental training conditions will show larger pre-post improvements in working memory, inhibitory control, reasoning, and everyday cognitive functioning than participants in the active control condition.

#### Hypothesis 4

(attentional control demands): Compared to the active control condition, experimental training conditions with stronger attentional control demands will induce larger near and far transfer effects. Specifically, transfer effects will be largest after dual task training, followed by switching training, and, lastly, choice RT training.

#### Hypothesis 5

(underlying mechanism): Training-induced changes in drift rate in the experimental training conditions relative to the active control condition predict the size of near and far transfer effects, and the relationship between training-induced change in drift rate and the size of transfer effects will be stronger with increased attentional control demands of the training condition. Specifically, we expect this relationship to be strongest after dual task training, followed by switching training, and, lastly, choice RT training.

## Method

This study protocol is preregistered on the Open Science Framework at https://osf.io/j5g7e.

### Design

Table 1 provides an overview of the study design. This multi-site, longitudinal, double-blinded, and actively controlled study uses a mixed 4 (training condition, between-subjects: simple RT, choice RT, task switching, and dual task training) × 3 (time, within-subjects: pretest, posttest, follow-up) factors design with age as covariate.

**Table 1 Tab1:** Schedule of enrollment, assessments, and interventions

Measure	Study phase and timepoint									
	Pre-assessment	Pretest				Intervention	Posttest		Follow-Up	
	T0–P	T0–Q	T1–V1	T1–V2	T1–R	S1–S10	T2–V1	T2–V2	T3–V1	T3–V2
*Enrolment*										
Eligibility screening and conditional enrolment	X									
Informed consent^a^		X	X							
MoCA assessment, confirmation of eligibility, and final enrolment			X							
Randomization					X					
*Interventions*										
Active control: Simple RT						X				
Experimental—low: Choice RT						X				
Experimental—medium: Switching						X				
Experimental—high: Dual tasking						X				
*Assessment of Training and Near Transfer Gains*										
Simple RT tasks (drawings, shapes, numbers)				X				X		X
Choice RT tasks (drawings, shapes, numbers)				X				X		X
Switching tasks (drawings, shapes, numbers)				X				X		X
Dual tasks (drawings, shapes, numbers)				X				X		X
*Assessment of Far Transfer Gains*										
Working memory										
Updating			X				X		X	
Binding			X				X		X	
Continuous reproduction			X				X		X	
Inhibitory control										
Go/no-go			X				X		X	
Number stroop			X				X		X	
Simon			X				X		X	
Reasoning										
Matrix reasoning			X				X		X	
Paper folding			X				X		X	
Letter sets			X				X		X	
Everyday cognitive functioning										
Cognitive Failures Questionnaire (CFQ)			X				X		X	
Questionnaire d’Auto-évaluation de la Mémoire (QAM)			X				X		X	
Everyday Problems Test (EPT)			X				X		X	
*Assessment of Individual Characteristics*										
Socioeconomic background		X								
Cognitive training experience and motivation		X								
Computer and internet literacy		X								
Self-rated physical health		X								
General self-rated health			X				X		X	
Depression, Anxiety and Stress Scale—21 Items (DASS-21)		X								
Activities of Daily Living-Prevention Instrument (ADL-PI)			X				X		X	
Leisure activities		X								
Active driving		X								
Big Five Inventory (BFI)		X								
Short Grit Scale (Grit-S)		X								
Theories of Intelligence Scale (TIS)			X				X		X	
Exercise Self-Efficacy Scale (EXSE)		X								
General Self-Efficacy Scale (GSE)			X				X		X	
Perceived training benefits										X
Training review										X
Daily factors			X	X		X	X	X	X	X

*T* time, *P* phone screening, *Q* questionnaires, *V* visit to the laboratory, *R* randomization, *S* session, *MoCA* Montreal Cognitive Assessment, *RT* reaction time

^a^Participants in Sheffield will give consent online before completing the pre-assessment questionnaires, and participants in Hamburg and Montréal will give consent at their first visit to the laboratory

To test our hypotheses, we will compare three experimental training interventions with systematically increasing attentional control demands to an active control group practicing tasks involving only minimal attentional control demands. Participants ranging in age from young to old adulthood (18–85 years) will complete 10 sessions of either simple RT (active control), choice RT (training with low attentional control demands), switching (training with medium attentional control demands), or dual task training (training with high attentional control demands). We will assess near transfer to the respective other training tasks and far transfer to working memory, inhibitory control, reasoning, and everyday cognitive functioning before, immediately after, and three months after training (i.e., pretest, posttest, and follow-up, respectively). All training groups will undergo the same study procedures and be exposed to the same task materials, with the active control group serving as baseline for training-related changes in the cognitive abilities tested at pretest, posttest, and follow-up.

### Timeline

Figure 2 provides an overview of the study’s timeline. Participation in this study will span approximately four months. After study sign-up and a phone screening confirming eligibility, participants will complete a set of short questionnaires from home at any time before their first visit to the laboratory (pre-assessment questionnaires). Each pretest, posttest and follow-up assessments consist of two test sessions (approximately 2 h each) that are completed within one week in the research laboratories of the participating institutions. After the second pretest session, participants will be asked to complete ten training sessions at home, each taking approximately 30 min, over the course of two weeks. Participants will complete the two posttest sessions in the following week and the two follow-up assessments three months later.

**Fig. 2 Fig2:**
[figure not shown]
Study Timeline. *Note*. Dashed lines indicate elements of the study that participants (18- to 85-year old healthy adults) complete from home, and solid lines indicate study elements that participants complete in the laboratory at one of the three respective study sites (University of Sheffield, Medical School Hamburg, and Centre de Recherche de l’Institut Universitaire de Gériatrie de Montréal, CRIUGM)

### Participants

Participants will be recruited from local communities for a study on “brain training” (German: “Übungen zum Gehirntraining”; French: “exercices pour stimuler le cerveau”) through a range of sources such as posters, leaflets, social media (e.g., Facebook, Twitter), outreach events (e.g., public lectures), ads in newspapers, and existing participant pools. Participants will be reimbursed after study completion (GBP 125 in Sheffield, EUR 150 in Hamburg, and CAD 250 in Montréal) or pro rata in case they withdraw consent and/or drop out of the study (GBP 12.50, EUR 15, or CAD 25, respectively for each visit, and GBP 50, EUR 60, or CAD 100 respectively, for completing the training phase). Psychology students at the University of Sheffield and the Medical School Hamburg can choose to receive a mix of course credits and monetary compensation. This study has been ethically approved by the institutional review boards at each of the three research sites. All participants will have provided written informed consent and have the right to withdraw from the study at any time until participation completion without any negative consequences.

#### Inclusion and exclusion criteria

Participants will self-report whether they meet the inclusion and exclusion criteria during a pre-scripted phone screening, except their score in the Montreal Cognitive Assessment [MoCA; 31]. The MoCA (version 8.1) will be administered as a pen-and-paper test at the beginning of the first pretest session.

Inclusion criteria:Age: 18–85 years oldAccess to a computer/laptop with internet connectionFluency in English (Sheffield), German (Hamburg), or French (Montréal), respectivelyBe in good health, that is, feeling physically fit to participate in the study and not currently diagnosed with any illness(es) that may limit their ability to participate in this studyCommitment to take part in the entirety of the study, that is, willing to invest 1 month of active participation and a follow-up assessment 3 months later, with a total of 6 visits at the respective testing center

Exclusion criteria:MoCA score below 26^1^Color blindnessDaily use of drugs (e.g., cannabis) and/or consumption of more than about one glass of alcohol (Sheffield: 25 units per week; Hamburg: 1 glass daily; Montréal: 1 unit daily)Knowledge of a current diagnosis with disease(s) that may limit participation in this study, including neurodegenerative diseases or dementia, neurological disorders, mental illness, other disease diagnoses known to the subjects which may impact the ability to take part in the study and/or knowledge of other brain diseases that may affect cognition and/or motor function of the handsCurrently participating in another research project that could interfere with this projectPrevious participation in a research project on memory and/or cognitive training that could interfere with this project

#### Sample size

We aim for a total sample size of at least 400 participants (*n* = 100 per condition) recruited across the three sites. To account for stratification (see below), our goal is to recruit *n* = 136 participants per site (*N* = 408). Based on previous cognitive training studies, training effects tend to be very large, whereas transfer effects tend to be small. The required sample size to achieve 80% power at α = 0.05 for a small effect size (Cohen’s *f* = 0.10) is *N* = 280 for a main effect of condition on change in transfer measures from pretest to posttest. However, in this study, an additional aim is to determine how changes in cognitive processes during training (i.e., the diffusion model parameters) relate to changes in the transfer measures using multi-group latent-change score models, a structural-equation modeling technique. Currently, no empirical simulation studies exist offering guidelines for optimal sample sizes [32]. We therefore estimated the required sample size based on previous studies using similar techniques [33, 34] and general power considerations for correlational designs. According to simulation studies [35], correlations of *r* = 0.24, as are typically found for the relationship between processing speed and fluid intelligence [11], tend to stabilize at sample sizes between *N* = 304 to *N* = 341 (90% power, corridor of stability w = 0.10). The total sample size of *N* = 408 participants will allow for some attrition (~15 to 20%).

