#### Hypothesis 5 (underlying mechanism)

To test whether training-induced changes in drift rate predict near and far transfer, we will combine the latent-change models for training and transfer domains and use the latent change in the training domain as predictor of the latent change in the transfer domain. We will compare (1) each experimental condition separately to the active control condition, and (2) the experimental conditions to each other. We expect that training-induced changes in drift rate are most strongly related to the size of transfer effect relative to the active control conditions if acquired in a training context with relatively higher attentional control demands (i.e., dual task > switching task > choice RT task). If the multigroup models fail to converge, we will attempt modeling the relationships for each group separately and for all groups together.

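### The 304–341 stability figure behind the sample size is for one pooled correlation; Hypothesis 5 compares slopes between arms of about 82–102, and '90% power' is a mislabel

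*Protocol article*

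**What the plan says.** The Sample size section aims for "at least 400 participants (*n* = 100 per condition") and sets a recruitment goal: "our goal is to recruit *n* = 136 participants per site (*N* = 408"). For the aim of linking change in diffusion parameters to change in transfer measures with multi-group latent-change models, it acknowledges that no simulation guidance exists. It then relies on two bases: earlier studies with similar techniques, and general power considerations for correlational designs. The second basis is the only one with numbers: "correlations of *r* = 0.24, as are typically found for the relationship between processing speed and fluid intelligence" are said to "tend to stabilize at sample sizes between *N* = 304 to *N* = 341" ("90% power, corridor of stability w = 0.10"). The total of 408 "participants will allow for some attrition (~15 to 20"%).

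Hypothesis 5 has two parts. Change in drift rate should predict transfer, and this relation should be stronger the higher the attentional control demands of the training (dual task, then switching, then choice RT). The analysis section for Hypothesis 5 regresses latent transfer change on latent training change and states: "We will compare (1) each experimental condition separately to the active control condition, and (2) the experimental conditions to each other". If the multigroup models fail to converge, "we will attempt modeling the relationships for each group separately and for all groups together".

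**The concern.** A stability figure describes how many people one sample needs before its correlation stops wandering. Here it is set against the total of all four arms, while the planned tests use each arm's own slope and the differences between slopes. Each arm holds a quarter of the total, and a difference between two slopes is less precise than either slope alone. A reader who takes the 90% at face value would think that Hypothesis 5 is well supported throughout.

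The relation between drift-rate change and transfer is the study's mechanism question. If the between-arm part is imprecise and the plan does not say so, an observed ordering of the three arms could be mostly noise, and non-significant differences could be read as equal mechanisms.

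**Working it through.** **Inputs.** From Sample size: r = 0.24; w = 0.10; 90%; 304–341; total 408; attrition 15–20%. From Randomization: blocks of four assignments, so equal arms. Assumed here: two-sided 0.05 for the correlation checks (the article gives α = 0.05 only for its f = 0.10 calculation), observed rather than latent correlations, and the sizes of the differences between arms.

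**1. Reproducing 304–341.** The check simulates 20,000 bivariate-normal trajectories from one sample, n = 20 to 1000, with a corridor of ρ ± 0.10. It takes the 90th percentile of the point after which the estimate no longer leaves the corridor:
- ρ = 0.20: 344
- ρ = 0.24: 329
- ρ = 0.30: 308

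The stated range is therefore the one-sample result for correlations of about 0.30 down to 0.20. The figure is sound for one pooled sample.

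**2. The label.** With the Fisher z transformation, power to detect r against zero is approximately Φ(atanh(r)·√(n − 3) − 1.96), and atanh(0.24) = 0.245. At n = 304–341 this gives about 99%. Power of 90% would need only about 179 people. So the 90% is confidence of stability, not power.

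**3. Arm size.** 408/4 = 102. After 15% loss 86.7, and after 20% loss 81.6 (about 82).

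**4. Precision within one arm at r = 0.24.** The 95% interval is tanh(0.245 ± 1.96/√(n − 3)).
- n = 102: standard error 1/√99 = 0.101; interval 0.05 to 0.42
- n = 82: standard error 1/√79 = 0.113; interval 0.02 to 0.43

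In the same kind of simulation, about 47% of trajectories are stable by n = 102 and 37% by n = 82, against the stated 90%.

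**5. Differences between two arms.** The standard error of the difference in z is √(2/(n − 3)) = 0.142 (n = 102) or 0.159 (n = 82).

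| Comparison | n = 82 per arm | n = 102 per arm |
|---|---|---|
| Power, 0.24 vs 0 | 34% | 41% |
| Power, 0.24 vs 0.14 | 10% | 11% |
| Power, 0.34 vs 0.24 | 11% | 12% |
| Difference in z detectable at 80% power | 0.45 | 0.40 |
| Same, as r in the other arm when one arm is 0.24 | 0.60 | 0.57 |

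The detectable difference is (1.96 + 0.84) × standard error. For 80% power on 0.24 vs 0, about 266 per arm would be needed.

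**6. Attrition.** 408 × 0.85 = 347 and 408 × 0.80 = 326. Both are at or above the lower end of 304–341, and 326 is close to the 329 simulated for r = 0.24. About 90% of trajectories are stable at n = 326 for that r.

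**The case against.** Several points on the other side are fair.

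- **No figure is miscalculated.** The 304–341 range reproduces. The fault is that the justification does not fit the test, and that one label is wrong.
- **The stability figure is not the only basis.** The article also cites earlier studies with similar techniques, which cannot be checked here. It is open about the lack of simulation guidance, and it claims no power for a slope difference in so many words. This softens the point. It does not make a pooled figure apply to arms.
- **Hypothesis 5 has a pooled reading.** Its first part, that drift-rate change predicts transfer, could be answered across conditions, and 304–341 would then be relevant. But the analysis section names a fit of all groups together only after non-convergence.
- **The power figures are approximations.** The planned tests use latent change, model comparison and Bayes factors, with values between 0.33 and 3 treated as ambiguous. Exact values will differ, but not plausibly enough to lift 10–41% to a conventional 80%.

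A reader might also infer that the attrition allowance fails, because 326 is below 341. The documents do not support that. The article gives a range, 326 lies inside it, and its upper end corresponds to a correlation near 0.20 rather than the stated 0.24. At 0.24, a 20% loss still gives about 90% stability in the pooled sample.

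Finally, a reader might conclude that one common slope must become the primary test. That is debatable: Hypothesis 5 predicts unequal slopes, and the trained domain differs by arm.

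**Conclusion.** The point holds as a mismatch between the sample-size justification and the between-arm part of Hypothesis 5, together with a wrong label. The 304–341 figure supports a relation pooled across conditions. For single arms of about 82–102, stability is 37–47% rather than 90%. Two-arm comparisons have about 34–41% power for 0.24 vs 0 and 10–12% for a difference of 0.10. Only very large contrasts, such as 0.57–0.60 against 0.24, reach 80%.

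These sizes rest on observed correlations, two-sided 0.05 and assumed arm differences. They also carry over the article's r = 0.24, which describes processing speed and fluid intelligence rather than change with change. The direction of the conclusion does not depend on the exact values. The total sample size and the attrition allowance are not shown to be wrong. The correction should be made, but it is one of statement and interpretation.

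**What to change.** In Sample size:
- State that 304–341 supports only a relation pooled across conditions.
- Replace the 90% power label with 90% confidence of stability.
- Restate the justification for Hypothesis 5 with the expected interval per arm (for r = 0.24, about 0.05–0.42 at n = 102 and 0.02–0.43 at n = 82) and the between-arm slope difference detectable at 80% power (about 0.57–0.60 vs 0.24), noting that these are approximations.

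In the analysis section for Hypothesis 5:
- Report arm-specific slopes and their differences with intervals.
- State that a non-significant difference will not be read as equal slopes.
- Optionally, add a pooled slope or a single ordered-trend test across the arms. A pooled slope would need a statement of which trained domain supplies the predictor in each arm.

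The cost is a few sentences, with no change to recruitment. The downside is that the stated precision for the between-arm part of Hypothesis 5 becomes less favourable.
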